### Variables and sources of information

#### Main variable: Consumption of resources

##### Primary and specialised care

Records of patient activity will be obtained from Osakidetza’s information systems.

The variables for analysis are the following:

- Number of nursing home visits.

- Number of visits to nursing home health clinics.

- Number of home visits by the family doctor.

- Number of visits to the family doctor’s clinic.

- Number of specialist outpatient consultations.

- Number of visits to hospital emergency departments.

- Number of hospital admissions.

- Number of days admitted to hospital.

##### Home hospitalisation

A formula will be designed to record the daily activity of Home Hospitalisation professionals during the period of care.

Variables to record:

- Number of visits by Home Hospitalisation.

- Number of calls to Home Hospitalisation.

- Grieving process (depending on the activity undertaken during the period).

◦ Number of bereavement support visits.

◦ Number of bereavement support calls.

### SAIATU

A model will be designed to record the daily activity of SAIATU professionals, which will allow researchers to keep track of activity during the progression of the disease and throughout the grieving process.

Variables to be recorded:

- During the progression of the illness:

◦ Number of visits by SAIATU.

◦ Number of calls from SAIATU.

- During the grieving process:

◦ Number of bereavement support visits by SAIATU.

◦ Number of bereavement support calls by SAIATU.

### Costs of care

The cost of SAIATU’s activities will be estimated by reference to budgetary information. Cost estimates for Hospitals, Primary Care, Home Hospitalisation and Palliative Care will be arrived at by multiplying costs by the quantity of resources consumed by each patient.

Where budgetary information about the activities of Hospitals, Primary Care and Home Hospitalisation is available, a calculation will be made multiplying costs by the quantity of resources consumed by each patient.

Secondary variables:

- Socio-demographic data.

- Place of death: home or hospital.

- Level of functional dependency: Karnofsky index <50.

- Characterisation of the principal carer.

- Quality of care in Palliative Care, measured according to the Palliative Outcome Scale and validated in Spanish [27].

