**Method/design:**

Comparative prospective cohort study, with randomised selection of patients, which will systematically measure patient characteristics and their consumption of resources in the last 30 days of life, with and without the intervention of a social support team trained to provide in-home end-of-life care.

For a sample of approximately 150 patients, data regarding the consumption of public healthcare resources, SAIATU activity, home hospitalisation teams, and palliative care will be recorded. Such data will also include information dealing with the socio-demographic and clinical characteristics of the patients and attending carers, as well as particular characteristics of patient outcomes (Karnofsky Index), and of the outcomes of palliative care received (Palliative Outcome Scale).

Ethical approval for the study was given by the Clinical Research Ethics Committee of Euskadi (CREC-C) on 10 Dec 2012.

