#### Phase 1: RETROSPECTIVE study to register a control cohort of patients who died from malignant neoplasm

The objective of this study is to determine the baseline risk of the principal variable, *consumption of resources* in the population of patients who die from malignant neoplasm.

Thus, the study characterises, by primary diagnosis (criteria and rules established by the International Statistical Classification of Diseases 10 [ICD-10] [26]) and age, the behaviour of different malignant neoplasms, with regard to resource consumption: number of visits to or consultations with Primary Care, number of external consultations, number of visits to hospital emergency departments, number of hospital admissions, average length of stay, and days in home hospitalisation.

Time of study: time series of 4 years, to be determined based on Osakidetza records and the mortality register.

Based on the results of this study and on the hypothesis of the decrease in, and improved efficiency of, resource consumption through the intervention of support programs, formulated as a result of the retrospective observational study carried out, the sample size of cohorts and subgroups will be defined for Phase 2: PROSPECTIVE cohort study.

For this analysis, the error will be established at α = 5% with a statistical significance of 80% (error β = 20%). The sample size of each subgroup *n* will be the maximum of the sample sizes obtained for the comparison of means or proportions of the main variables in each subgroup.

For the comparison of two means:

(1)$$n\;=\;\left(2\left[\left(\mathrm{Z\alpha}/2+\mathrm{Z\beta}\right)\right]\wedge 2*\text{S}\wedge 2\right)/\text{d}\wedge 2$$

where:

(2)$$\begin{array}{l} \mathrm{Z\alpha}/2\;=\;1.960\\ \mathrm{Z\beta}\;=\;0.842 \end{array}$$

S^2^ = variance in the quantitative variable of the control group

d = Minimum value of the difference to be detected (quantitative values)

For the comparison of two proportions:

(3)$$n\;=\;2p*q\wedge 2\left(\mathrm{Z\alpha}/2+\mathrm{Z\beta}\right)\wedge 2/\left(\mathrm{pA}-\mathrm{pB}\right)\wedge 2$$

where:

(4)$$\begin{array}{l} \mathrm{Z\alpha}/2=1.960\\ \mathrm{Z\beta}=0.842 \end{array}$$

p = Mean of the two proportions pA y pB

The parameters will be analysed with the statistical software SPSS 15.0 for Windows.

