#### Phase 2. Study of PROSPECTIVE cohorts, assigned by randomised blocks

The study will be initiated with two cohorts:

1.
***Exposed cohort*****:** comprising patients who will be attended by SAIATU, without prejudice to the care received from the public health system.

2.
***Control cohort*****:** comprising patients who will be cared for exclusively through the public health system.

The evolution of the disease over the course of the study will determine the different healthcare mechanisms (Primary Care, Specialised Care (SC), Home Hospitalisation (HH)) that will intervene in the care of each patient, so that, at the end of the study, the two initial cohorts will be divided into 4 subgroups:

1)
*Exposed cohort*

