### Population for Study

This study will comprise oncology patients from the health districts of Guipúzcoa, attended by the Basque Health Service.

Assuming that 2,500 people per million population die each year from malignant neoplasm, and taking into account that the population of Guipúzcoa is 709,607 inhabitants, it is estimated that the eligible population for this study is 1,774 deaths from malignant neoplasm per year. For a period of 10 months of prospective study, this corresponds to a population of 1,478 deaths from malignant neoplasm in these provinces.

Although the final number of patients for inclusion will be calculated during the design of the prospective study itself, after the results of Phase 1, it is estimated that the resulting sample size could allow some 150 patients to be studied. This sample, which would correspond to 10% of the total population of deaths from cancer in this period, would strengthen the study’s feasibility with respect to its representativeness of the total population in both provinces.

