### Analysis of variables

The parameters will be analysed using the statistical software SPSS 15.0 for Windows.

A descriptive study will be conducted on the *consumption of healthcare resources* by subgroup in the last 30 days of life. The descriptive study will include measures of central tendency, confidence intervals at 95% for the population mean, and contingency tables (frequencies) for each of the recorded variables.

Each subgroup will be analysed by age, sex, and main diagnosis.

For the comparison of proportions, Pearson’s Χ^2^ test, or, when appropriate, Fisher’s exact test will be used to calculate relative risk (RR), absolute risk reduction (ARR) and the number needed to treat (NNT) with 95% confidence interval.

The Student T-test will be applied to calculate the equality of means for independent samples in the case of continuous variables, upon confirmation of the conditions of normality and homoscedasticity.

The quantification of costs incurred by the SAIATU program will be calculated on the basis of the activities performed by the program’s professionals, measured in hours of care. Based on the actual time spent on patients, the total cost will be distributed between each of the activities.

Calculations of unit costs per activity, taking into account the number of times each activity is performed for the period under analysis, will finally be performed.

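### The methods define the Karnofsky variable only as a cut at <50; if that cut is what is compared, at least about a third of the score's information is lost

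*Protocol article*

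**What the plan says.** The secondary variables are listed at the end of the section Costs of care. The entry for function reads "Level of functional dependency: Karnofsky index <50". No other definition of a Karnofsky variable appears in the methods, and no reason is given for 50.

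The abstract (Method/design) describes the data to be recorded and includes "particular characteristics of patient outcomes (Karnofsky Index", with no threshold.

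The section Analysis of variables offers two comparison routes. For binary variables: "For the comparison of proportions, Pearson’s Χ^2^ test, or, when appropriate, Fisher’s exact test will be used". For continuous variables: "The Student T-test will be applied to calculate the equality of means for independent samples in the case of continuous variables", provided that normality and equal variances are confirmed. Karnofsky is not assigned by name to either route. The same section promises summaries of central tendency and frequencies for the recorded variables.

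**The concern.** The abstract speaks of an index and the methods of a threshold. A variable defined as below 50 or not is a proportion, so a reader who follows the methods would compare the cohorts by chi-square or Fisher's exact test. That treats a patient at 40 and a patient at 10 as the same, and any change in function that does not cross 50 is invisible.

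At stake is the sensitivity of one secondary comparison between patients with and without the SAIATU program. The population makes the position of the cut relevant. These are patients with advanced, incurable cancer, described over their final 30 days, and the further the scores lie from 50 on one side, the less a cut there separates them.

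**Working it through.** **The plan's own figures.** The article states no mean, standard deviation, proportion or power for Karnofsky, so there is no Karnofsky figure to reproduce. The figures used below do reproduce:

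- Population for Study: 2,500 × 0.709607 = 1,774 deaths per year; 1,774 × 10/12 = 1,478; 150/1,478 = 10.1%, given as 10%.
- Phase 1: α = 5% two-sided and β = 20%, so z = 1.960 and 0.842, with sum 2.802.

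**Inputs.**

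- Total size: "it is estimated that the resulting sample size could allow some 150 patients to be studied". The article calls this provisional until Phase 1 is complete.
- Allocation: "The study will be initiated with two cohorts", with no ratio given. Assumed 1:1, so n = 75 per cohort.
- Share of patients below 50, p: not given. Shown as a range.
- Score model: normal with a shift between cohorts (assumed).

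**Step 1. Efficiency of a cut relative to the full score.**

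RE = φ(z_p)² / [p(1 − p)], where z_p is the normal quantile of p.

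At p = 0.50: 0.3989² / 0.25 = 0.1592 / 0.25 = 0.637. This is the maximum, so the smallest possible loss under this model is 36%.

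**Step 2. Where the loss passes one half.** Solving RE = 0.50 gives p = 0.79 (or, by symmetry, 0.21).

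**Step 3. Power at 75 per cohort.** The difference that the full score detects with 80% power is d = 2.802 × √(2/75) = 0.457 SD. With c = z_p, the proportions below 50 in the two cohorts are p1 = Φ(c + d/2) and p2 = Φ(c − d/2). The power of the comparison of proportions, with p̄ the mean of p1 and p2, is

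Φ{ [ |p1 − p2| − 1.960 √(2p̄(1 − p̄)/n) ] / √([p1(1 − p1) + p2(1 − p2)]/n) }.

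At p = 0.50, p1 = 0.590 and p2 = 0.410, and the power is 60%. The short form Φ(2.802 √RE − 1.960) = Φ(2.236 − 1.960) gives 61%, in agreement.

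| Share below 50 (assumed) | RE | Information lost | Power with the cut | n per cohort for 80% |
|---|---|---|---|---|
| 0.50 | 0.637 | 36% | 60% | 119 |
| 0.70 | 0.576 | 42% | 56% | 132 |
| 0.80 | 0.490 | 51% | 49% | 157 |
| 0.90 | 0.342 | 66% | 36% | 227 |
| 0.95 | 0.224 | 78% | 25% | 352 |

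**Step 4. Allowing for a score in steps of 10.** The same comparison was made against a score grouped in tens, with assumed means and SDs of 10 and 15. For means of 40 to 50 the RE is 0.63 to 0.69, so 31% to 37% is lost. For a mean of 30 it is 0.47 (SD 15) to 0.29 (SD 10), so 53% to 71% is lost. The loss of about a third is therefore not an artefact of treating the score as continuous.

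**The case against.** The strongest reply is that the line at issue is one entry in a list of variables and not an analysis rule. The abstract says that the index is recorded, the analysis section provides for continuous variables as well as proportions, and nothing says that the score will be dropped. The entry may only label which patients count as functionally dependent. The objectives and hypothesis concern resource use, cost and quality of life, and none names a comparison of functional status. Coding of a secondary scale is also often left to a fuller document.

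Much of this stands. It makes the point conditional (it applies if the cut is the analysed variable) and keeps it minor. It does not remove it. The article does more than leave the coding open: it fixes a threshold as the only definition in its methods, and that definition leads to the tests for proportions.

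Three stronger readings are tempting and are not supported:

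- A reader might infer that the cut discards most of the information. That needs about 79% or more of patients on one side of 50. The article gives no score distribution, no Karnofsky entry criterion and no time of assessment. A large share below 50 is plausible close to death, but it remains an assumption.
- A reader might infer that adjustment of the resource comparison is weakened. The analysis section describes no covariate-adjusted model.
- A reader might infer that the full score must be on file because the cut requires it. The abstract makes this likely, but the article does not say so, and an assessor could mark below 50 directly.

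**Conclusion.** The point holds in conditional form and is a minor, nearly free improvement. The methods define Karnofsky only as <50, while the abstract names the index. If the cut is what is compared, about a third of the information is lost at best, and power is about 60% where the full score would have 80%. The loss exceeds one half only if about 80% or more of patients are below 50 (or about 20% or fewer).

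These sizes rest on a normal shift, 75 patients per cohort from a provisional total of about 150, and a difference chosen so that the full score has 80% power. The trial's sample size is to be set on its main variables, so neither that size nor the main resource comparison is affected.

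**What to change.** In the list of secondary variables, define the item as the Karnofsky index, recorded and compared between cohorts as its full ordinal score (0 to 100 in steps of 10). Name the comparison in the section Analysis of variables: a rank test, or a comparison of scores. Keep <50 only as a descriptive percentage per cohort. This also brings the methods into line with the abstract.

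The cost is a change of wording. If the form now collects only below 50 or not, the field must take the score instead. The assessment is the same.

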### Analysis of variables

The parameters will be analysed using the statistical software SPSS 15.0 for Windows.

A descriptive study will be conducted on the *consumption of healthcare resources* by subgroup in the last 30 days of life. The descriptive study will include measures of central tendency, confidence intervals at 95% for the population mean, and contingency tables (frequencies) for each of the recorded variables.

Each subgroup will be analysed by age, sex, and main diagnosis.

For the comparison of proportions, Pearson’s Χ^2^ test, or, when appropriate, Fisher’s exact test will be used to calculate relative risk (RR), absolute risk reduction (ARR) and the number needed to treat (NNT) with 95% confidence interval.

The Student T-test will be applied to calculate the equality of means for independent samples in the case of continuous variables, upon confirmation of the conditions of normality and homoscedasticity.

The quantification of costs incurred by the SAIATU program will be calculated on the basis of the activities performed by the program’s professionals, measured in hours of care. Based on the actual time spent on patients, the total cost will be distributed between each of the activities.

Calculations of unit costs per activity, taking into account the number of times each activity is performed for the period under analysis, will finally be performed.

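### The named tests are unadjusted, and age, sex and diagnosis only break down four small subgroups; one adjusted comparison of the assigned cohorts would use the data better

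*Protocol article*

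**What the plan says.** The section *Analysis of variables* gives Student's t-test for continuous variables, subject to checks of normality and equal variance. For proportions it gives Pearson's chi-square or Fisher's exact test. No covariate, block term or interaction is mentioned.

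Age, sex and diagnosis appear in that section once: "Each subgroup will be analysed by age, sex, and main diagnosis". The subgroups come from the Phase 2 design, where "the two initial cohorts will be divided into 4 subgroups", according to cohort and whether home hospitalisation took part in care. The course of the disease after assignment decides the latter.

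Three other places bear on the point:

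- Allocation is described in a heading, "Study of PROSPECTIVE cohorts, assigned by randomised blocks". What the blocks are formed on is not stated.
- Phase 1 describes, by primary diagnosis and age, "the behaviour of different malignant neoplasms, with regard to resource consumption". The first of the *Specific objectives* asks for the same description.
- On size, *Population for Study* says "it is estimated that the resulting sample size could allow some 150 patients to be studied", with the final number to follow Phase 1. Under Phase 1, the sample size of each subgroup "will be the maximum of the sample sizes obtained for the comparison of means or proportions of the main variables in each subgroup".

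**The concern.** The plan expects diagnosis and age to be worth separating when describing resource use, but it does not use them in the comparison of patients with and without the programme. Outcome variation that these variables explain then stays in the error term and makes the treatment comparison less precise than it need be. Splitting on the same variables does not recover that precision, because each slice is a smaller unadjusted comparison.

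Two things are at stake. One is power for the main question, in a study whose size was put forward as a feasible share of deaths. The other is interpretation: estimates from slices of a dozen patients or fewer are unstable and easily over-read unless they are labelled as descriptive.

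**Working it through.** **Inputs.** From the article: population 709,607; 2,500 cancer deaths per million per year; a 10-month prospective period; about 150 patients; four subgroups; α = 5% two-sided (z = 1.960); β = 20% (z = 0.842). Assumed, because not given: 1:1 allocation, equal subgroups, the numbers of age and diagnosis categories, and the share of variance R² that the covariates explain. The detectable difference and SD are to come from Phase 1, so effects are in SD units.

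**The plan's own figures.** 709,607 × 2,500 / 1,000,000 = 1,774 per year. 1,774 × 10/12 = 1,478. 150 / 1,478 = 10.1%. All agree with *Population for Study*. The 150 is thus a share of deaths and cannot be rebuilt from the sample-size formula.

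**Size of the slices.** 150 / 4 = 37.5 per subgroup. Taking one factor at a time:

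- sex: 37.5 / 2 = 18.75
- age, 2 to 4 groups (assumed): 18.75 down to 9.4
- diagnosis, 3 to 8 groups (assumed): 12.5 down to 4.7

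**What such groups can show.** With n per group, the difference detectable with 80% power is (1.960 + 0.842) × √(2/n) SD. For 75 against 75 this is 2.802 × √(2/75) = 0.457 SD. Power for 0.457 SD at smaller n is Φ(0.457/√(2/n) − 1.960).

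| Exposed against control | n per group | Detectable (SD) | Power for 0.457 SD |
|---|---|---|---|
| Whole cohorts | 75 | 0.457 | 80% |
| Within home-hospitalisation status | 37.5 | 0.647 | 51% |
| and within one sex | 18.75 | 0.915 | 29% |
| and within one of 3 age groups | 12.5 | 1.12 | 21% |
| and within one of 5 diagnoses | 7.5 | 1.45 | 14% |

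The last three rows each split the 37.5 by one factor alone. If only 20 to 30% of each cohort received home hospitalisation (assumed), those subgroups would hold 15 to 22.5 patients per cohort, with power of 24 to 34% before any slicing.

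**If n is instead set per subgroup.** Suppose each subgroup has the n that gives 80% power for the chosen difference. A slice holding a fraction f of it has power Φ(2.802 × √f − 1.960). This gives 51% for f = 1/2, 37% for f = 1/3 and 24% for f = 1/5. Sizing by subgroup therefore does not cover the slices.

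**Gain from adjustment.** Adjustment multiplies the residual SD by √(1 − R²), so power becomes Φ(2.802/√(1 − R²) − 1.960). The equivalent unadjusted total is 150/(1 − R²).

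| R² (assumed) | Power | Equivalent unadjusted total |
|---|---|---|
| 0.10 | 84% | 167 |
| 0.20 | 88% | 188 |
| 0.30 | 92% | 214 |

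With age as one linear term, sex as one and five diagnosis groups as four, the model spends six parameters. Residual degrees of freedom go from 148 to 142, a small loss that the formula ignores. The formula is for a continuous outcome; for counts and for place of death the gain will differ.

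**The case against.** The strongest reply is that an unadjusted comparison of randomised cohorts is valid, so adjustment is a matter of efficiency, and that a condensed article may leave the model to a fuller document. The first half stands. The second has less force here, because the article does not leave the method open: it names the tests and states the role of the three covariates.

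It is also fair that the sentence on age, sex and diagnosis directly follows the descriptive paragraph. It may mean tables only. If so, it costs the main comparison no power, and the remedy for that part is to say so. The tests that follow remain unadjusted on either reading. The 150 is provisional, and Phase 1 reports no R², so the size of the gain is an assumption.

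Three stronger readings are tempting, and the document does not support them:

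- A reader might infer that the tests ignore prognostic strata and so have the wrong error rate. No blocking factor is named. These may be ordinary permuted blocks, and if a prognostic stratum were ignored the test would be conservative.
- A reader might infer almost empty cells and many chance findings. That needs all three factors crossed and particular category counts, and the text gives neither. It also specifies no tests within slices.
- A reader might infer that "Level of functional dependency: Karnofsky index <50" wastes a baseline covariate. It is listed as a secondary variable with no baseline time point, and nothing shows how patients would fall around the cut. Adjusting for a reading taken after assignment could itself bias the comparison.

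**Conclusion.** The point holds as an improvement in efficiency and not as an error of validity. The stated analysis leaves unused, in the main comparison, variables that the plan itself considers relevant to resource use, and applies them only to subgroups too small to support inference: about 37 patients each, and roughly 5 to 19 per slice at 150 in total.

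Adjustment would raise 80% power to about 84 to 92% if the covariates explain 10 to 30% of the variance. That range is conditional on the assumed R², 1:1 allocation and a continuous outcome. The slice sizes rest on equal splits and assumed category counts. That the slices lack power does not depend on the provisional 150, since it persists when n is set per subgroup.

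**What to change.** In *Analysis of variables*:

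1. Make the main analysis one comparison of the two cohorts as assigned, in a regression model suited to each outcome: a count model for visits, admissions and days; a model suited to skewed data for costs; a binary model for place of death, with results still expressible as the planned risk ratio, absolute risk reduction and number needed to treat.
2. Adjust each model for age, sex and diagnosis group, with the diagnosis grouping fixed in advance.
3. State what the blocks are formed on. Add that factor to the model if it is a patient or site characteristic; plain permuted blocks need no term.
4. Label the breakdowns by age, sex and diagnosis within the four subgroups as descriptive or exploratory.
5. Adjust for Karnofsky only if it is recorded at or before assignment.

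The cost is wording. Age, sex and main diagnosis are already planned for analysis, and no extra patients or visits are needed. Phase 1 can supply a rough R² for age, sex and diagnosis before the Phase 2 sample size is fixed, provided sex is recorded there, and would replace the range assumed above.

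### The t-test for the main variables is conditional on normality and equal variances; 30-day counts and costs will very probably fail the normality condition, and no alternative is named

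*Protocol article*

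**What the plan says.** All places are in the protocol article.

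- **Analysis of variables** gives the rule for means: the Student t-test for independent samples is to be used "in the case of continuous variables, upon confirmation of the conditions of normality and homoscedasticity". No other branch follows.
- The same section gives one other family of tests: "For the comparison of proportions, Pearson’s Χ^2^ test, or, when appropriate, Fisher’s exact test will be used", with relative risk, absolute risk reduction and number needed to treat.
- **Variables and sources of information**, under "Main variable: Consumption of resources", lists eight items. Each is a number of visits, consultations, admissions or days, for example "Number of hospital admissions" and "Number of visits to hospital emergency departments". None is a proportion.
- **Costs of care** obtains cost by "multiplying costs by the quantity of resources consumed by each patient".
- The **Hypothesis** and the analysis section both set the window at the final 30 days of life. Place of death, the clearly binary outcome, is a secondary variable.

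**The concern.** Counts of admissions or emergency visits over 30 days are small whole numbers, often zero. Hospital days in that window lie between 0 and 30. Cost is a weighted sum of such quantities and inherits their skew. Data of this kind rarely pass a normality check at the sample sizes foreseen, yet the plan makes the main comparison depend on passing one.

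Two things are at stake. First, if the condition fails, the analyst must choose a test after seeing the data, and the choice can change the answer. Second, the habitual replacement is a rank test. It does not estimate a difference in means, whereas the second specific objective is to quantify and compare costs, and the Discussion intends to project savings onto the whole Basque territory. Both need the difference in mean cost.

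**Working it through.** **Inputs from the article.** The planned sample is about 150 (Population for Study). The figures behind it reproduce: 709,607 × 2,500 / 1,000,000 = 1,774 deaths a year; 1,774 × 10/12 = 1,478 in ten months; 150 / 1,478 = 10.1%. Error rates are α = 5% two-sided (Z = 1.960) and β = 20% (Z = 0.842).

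**Assumptions.** The article gives no mean, standard deviation or share of zeros for any main variable, and no allocation ratio. I assume 75 per arm (1:1) and about 37 per group if each arm splits evenly into its two care subgroups. The article does not say how normality is to be confirmed; I use Shapiro-Wilk at 5%.

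**What the plan is sized on.** The formula for means is n = 2(Zα/2 + Zβ)² S² / d². Solving for the detectable difference gives d/S = 2.802 × √(2/75) = 0.458, or 0.651 with 37 per group. This already targets a difference in means.

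**Does the normality condition pass, and is the t-test sound without it?** Both arms are drawn from the same distribution: 1,000 pairs of arms for the normality check and 20,000 for type I error.

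| Assumed distribution | Both arms pass normality, 37 / 75 per arm | Type I error, pooled t-test, 37 / 75 per arm |
|---|---|---|
| Admissions: Poisson, mean 0.8 | 0% / 0% | 5.1% / 5.0% |
| Emergency visits: negative binomial, mean 1, k = 1 | 0% / 0% | 4.9% / 5.0% |
| Home visits: negative binomial, mean 3, k = 1 | 0% / 0% | 4.6% / 5.0% |
| Hospital days: 40% zeros, capped at 30 | 0% / 0% | 4.8% / 5.3% |
| Cost: log-normal, log-scale SD 1 | 0% / 0% | 4.4% / 4.2% |

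**Sensitivity to the assumed shapes.** A second set was tried: negative binomial with mean 1 (k = 5), 1.5 (k = 2), 9 (k = 0.8) and 4 (k = 1), and a log-normal cost. A single sample passed Shapiro-Wilk in 0% of 2,000 runs at 75, and in at most 0.2% at 37. Type I error of the pooled t-test was 4.4% to 5.2% at 75 per arm and 4.2% to 5.0% at 37. In this set hospital days are not capped, and 4.8% of patients exceed 30 days; the conclusion is the same.

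**Does the choice of test matter?** Assume that zeros in hospital days rise from 40% to 60% (mean about 5.7 to 3.8), with 75 per arm. The combined condition passed in 0% of 3,000 runs. Power was 36% for the t-test and 62% for the rank test. The effect here works entirely through the share of zeros, which suits a rank test, so the gap illustrates the point and is not a forecast.

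**Where the equal-variance form matters.** With equal means, unequal sizes and the larger variance in the smaller group, the pooled t-test had 9.9% type I error at 50 v 25 (Welch 7.3%) and 9.3% at 100 v 50 (Welch 6.1%). At 75 v 75 both were about 5.3%. The four subgroups are formed by care received, so their sizes may well differ.

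**The case against.** The strongest reply has four parts.

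1. *The t-test is sound on such data.* This stands. A reader might infer that the main hypothesis has no valid test; the simulations contradict that for equal arms. With equal arms Welch and Student share the same t statistic, so one cannot be accepted for skewed cost and the other rejected.

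2. *It is not the plan's only test.* This also stands: chi-square and Fisher are planned, and the sample size text foresees means or proportions of the main variables. But no main variable is defined as a proportion, so the conditional t-test remains the only stated test that fits them as listed.

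3. *An article may leave a fallback to the full protocol or analysis plan.* True of a missing detail. Here the article states a decision rule, and a later plan would have to replace that rule, not merely add to it. Descriptive means with 95% intervals are planned without any condition, which softens the loss, but no interval for the between-group difference is stated.

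4. *The size rests on assumptions.* It does. A looser check than Shapiro-Wilk, such as visual judgement, could pass more often, but would leave the choice to the analyst.

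Two further inferences should be resisted. The equal-variance condition does not block the test whenever there is an effect: under the second set of distributions at 75 per arm, Levene's test rejected in 17% to 45% of runs for a 25% reduction in the mean, and in 37% to 80% for a 40% reduction. Nor can one say that the test would be chosen after unblinding, because the article describes no blinding.

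**Conclusion.** The point holds in limited form. The stated rule ties the main comparison to a normality condition that counts, hospital days and costs will very probably fail, and gives no alternative. Read literally, no planned test would then be applicable to the main variables. Under every distribution tried, the condition passed in none or almost none of the samples at 37 and 75 per group. These distributions, the 1:1 split and the form of the normality check are assumptions; that the condition will fail is an inference from the type of variable, not a figure in the article.

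The documents do not support calling the t-test invalid. The harm lies in the pre-test, in a choice of method made after seeing the data, and in the risk of ending with a rank test that does not address mean cost. This should be corrected but does not undermine the design.

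**What to change.** In Analysis of variables, delete "upon confirmation of the conditions of normality and homoscedasticity". State instead that every resource count, hospital days and cost will be compared by the difference in arithmetic means with a Welch or bootstrap 95% confidence interval, whatever the distribution looks like. This matches the sample size formula for means and the cost objective.

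A count model, such as negative binomial regression with robust standard errors, may be added for visits and admissions. It is one reasonable option and not a necessity. Keep chi-square or Fisher for place of death.

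The cost is a change of wording and slightly more analysis work. If variances are in fact equal, Welch loses a negligible amount of power. Welch is not a complete cure in small, unequal subgroups (7.3% in the 50 v 25 example), so subgroup results would still need caution.
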